### Inclusion criteria

For inclusion in the study, all of the following inclusion criteria must be fulfilled: (i) pathologically confirmed colon adenocarcinoma (≥15 cm from the anal verge); (ii) assessment of *RAS* status of the primary colon cancer on biopsies (WT or mutated); (iii) CC classified by abdominal CT scan: high risk T3 (disruption of muscle wall and extension into pericolic fat with more than 5 mm protrusion into adjacent mesenteric fat) - T4 (penetration within adjacent organs) and/ or N2 (more than 3 clustered lymph nodes above 1 cm in shortest diameter); (iv) non metastatic CC (lung, liver, peritoneal); (v) non complicated primary tumor (obstruction, perforation, bleeding). Patients with obstructive CC and treated by defunctioning stoma can be included; (vi) absence of synchronous colorectal cancer ; (vii) age ≥ 18 years et ≤ 75 years; (viii) ECOG performance status 0–1 ; (ix) no prior chemotherapy or abdominal or pelvic irradiation; (x) life expectancy of ≥ 5 years; (xi) no history of colorectal cancer; (xii) patients with childbearing potential should use effective contraception during the study and the following 6 months; (xiii) laboratory data including : white blood cell count ≥ 3 × 10^9^/L with neutrophils ≥ 1.5 × 10^9^/L, platelet count ≥ 100 × 10^9^/L, hemoglobin ≥ 9 g/dL (5,6 mmol/l), total bilirubin ≤ 1.5 × ULN (upper limit of normal), ASAT and ALAT ≤2.5 × ULN, Alkaline phosphatase ≤1.5 × ULN, serum creatinine ≤ 1.5 × ULN; (xiv) signed written informed consent obtained prior to any study specific screening procedures.

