**Fig. 2 Fig2:**
[figure not shown]
The Tumor Regression Grade (TRG), as simplified to three categories by Ryan (19). TRG1: Major response; TRG2: Intermediate response; TRG3: No response

Secondary endpoints are the following: (i) postoperative morbidity (occurring within 60 postoperative days) graded 0 to 5 according to the Clavien-Dindo classification [20]. If grade 3 or 4 complications occur at a rate ≥ 10 % in either neoadjuvant chemotherapy arm, the arm will be declared hazardous (see section statistical analysis); (ii) the safety of neoadjuvant therapy will be assessed by the systematic collection of toxicity data related to chemotherapy, the total number of cycles administered pre-operatively (documenting reasons for early termination), and the systematic collection of GI symptoms. In addition, complications related to the in situ tumor that could delay the date of surgery or require emergency colonic surgery or stenting, will be documented. These parameters will be evaluated after administration of the first cycle of neoadjuvant chemotherapy; (iii) Regression-free survival at 3-years defined as the time interval between the date of randomization and the date of first recurrence (local, regional or metastatic) or date of death (all causes) if no recurrence; (iv) Disease-free survival at 3 years defined as the time interval between the date of randomization and the date of first recurrence (local, regional or metastatic), or second cancer, or the date of death without recurrence (all causes) and date of second cancer; (iv) Quality of life (evaluated using the EORTC quality of life (QoL) QLQ-C30 and QLQ-CR29); Quality of life will be assessed at the inclusion, after neoadjuvant chemotherapy, at 1 month after surgery and every 6 months thereafter. The QLQ-C30 consists of 30 items with both multi-items scales and single item measures. The internal validation of QLQ-C30 allowed to identify 15 scales and to generate 15 scores: 5 scores of functional scale (physical functioning, role functioning, cognitive functioning, emotional functioning, social functioning), a global health status scare, a financial difficulties scale and 8 symptoms scale (fatigue, nausea/ vomiting, pain, dyspnoea, insomnia, appetite loss, constipation, diarrhoea). These scores vary from 0 (worse) to 100 (better) for functional and global health scale and from 0 (better) to 100 (worse) for symptoms scales. Targeted QoL dimensions for this trial are Global Health, physical and emotional functioning, fatigue and pain of QLQ-30 as well as dimensions of CR29. A 5 points difference in QoL is considered as minimal clinically important difference (MCID). Time to QoL deterioration will be defined as time interval between randomization and first decrease in QoL score greater or equal to 5 points. Patients without QoL decrease greater or equal to 5 points will be censored at the last follow-up. (v) Quality and completeness of the surgical excision evaluated on pathological criteria (number of lymph nodes examined, the completeness of removed mesocolon, surgical margins); (vi) radiological staging and radiological response. The initial radiological staging based on abdominopelvic CT scan will be compared with the histopathological pTNM staging in the control group. CT scan images will be interpreted by the individual study centers, and reviewed by 2 of the 3 members of our Central Review Committee of Radiology. This dual independent reading will assess inter-observer reproducibility of the radiological response to treatment with a test of concordance. The radiological response will be defined by RECIST (v1.1) [21] on CT scan and evaluated in the neoadjuvant chemotherapy arms. These criteria will be applied to the primary colon tumors (largest diameter) and lymph nodes (smallest diameter). The sum of the diameters of the target lesions will be determined on the pretreatment CT scan (initial staging) and compared with the sum of these measures on the reevaluation CT scan (performed within 3 weeks after the completion of neoadjuvant chemotherapy). Interpretation of the reevaluation CT scan will be centralized and carried out independently by 2 of the 3 members of our Central Review Committee of Radiologists blinded to the pretreatment CT scan staging. This dual independent reading will assess inter-observer reproducibility of RECIST criteria applied to CC, and determine if there is a difference in radiological response between the two chemotherapy regimens under investigation in the study; (vii) Correlation between histopathological and radiological response. The radiological response of the primary tumor as defined by RECIST v1.1 criteria (taken for target lesion, only the primary tumor) will be compared with the histopathological response as defined by TRG-Ryan. Evaluation of this correlation will be centralized and carried out by the Central Review Committee of Radiology and Pathology; (viii) The 5-point regression grading system [22] adapted to CC by our team in a pilot study [15], will also be evaluated in this trial. This assessment will be centralized and carried out independently and blindly (without knowing the treatment arms) by 2 of the 3 members of our Central Review Committee of Pathology. This assessment will determine the inter-observer reproducibility of this grading system in CC after chemotherapy and to assess the specificity of histological "regression" criteria using this grading system. Comparison of the reproducibility (test of concordance) of the two systems of grading regression (TRG-Ryan and TRG-Mandard) will identify the most appropriate system for assessing response to chemotherapy in CC.

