## Discussion

There are several arguments in favor of performing a study to assess the impact on survival of perioperative chemotherapy in the treatment of stage II/III CC. Three prerequisites are however essential. First, systemic chemotherapy must be effective and able to induce a measurable and reproducible response of the primary tumor. Second, current preoperative imaging with abdominopelvic CT scan must allow for an accurate assessment of tumor stage to justify antineoplastic treatment with a limited number of false-positives patients in order not to over-treat patients that do not require such treatments. Finally, the neoadjuvant chemotherapy must be well tolerated and not increase the risk of pre- and post-operative complications.

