The aim of our phase II ECKINOXE study is to evaluate the efficacy (response rate) and tolerability of two regimens of neoadjuvant chemotherapy among patients with locally advanced CC. The control arm will consist of patients treated with FOLFOX-4 post-operatively. This study will allow us to investigate the feasibility and effectiveness of this original neo-adjuvant strategy, and to select the best regimen to improve long-term disease-free and overall survivals. A similar study testing another anti-EGFR monoclonal antibody (Panitumumab) is currently ongoing in the United Kingdom (FOxTROT trial). The pilot stage of this randomised controlled trial on the first 150 included has been recently published. Nearly 90 % (85 of 95) of patients in this trial completed preoperative chemotherapy with grade 3–4 gastrointestinal toxicity in 7 %. All 99 tumours in the preoperative group were resected, with no significant differences in postoperative morbidity between the preoperative and control groups. T3 or more advanced tumours was pathologically confirmed in 98 % of patients undergoing immediate surgery and 91 % of patients following preoperative chemotherapy (p = 0 · 10). Preoperative therapy resulted in significant downstaging in terms of TNM stage compared with the postoperative group (p = 0 · 04), including two pathological complete responses.

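### CT staging is checked against pTNM, which as used here cannot test the 5 mm depth rule that admits T3 tumours, so false positives against the entry definition are under-counted

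*Protocol article*

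**What the plan says.** Inclusion criterion (iii) defines the target population on CT. A tumour enters as high-risk T3 if there is "disruption of muscle wall and extension into pericolic fat with more than 5 mm protrusion into adjacent mesenteric fat". The other routes are "T4 (penetration within adjacent organs) and/ or N2 (more than 3 clustered lymph nodes above 1 cm in shortest diameter".

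Secondary endpoint (vi), under Endpoints, sets the check on that imaging: "The initial radiological staging based on abdominopelvic CT scan will be compared with the histopathological pTNM staging in the control group". Pre-therapeutic work-up says that the clinical TNM stage comes from the CT scan.

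The article names no pathological measurement of extramural depth. Under secondary endpoint (v), on quality of surgery, it lists "number of lymph nodes examined, the completeness of removed mesocolon, surgical margins".

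The Discussion names three essential prerequisites for the peri-operative strategy. One is CT staging accurate enough to justify treatment, with a "limited number of false-positives patients in order not to over-treat patients that do not require such treatments".

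**The concern.** A check on a selection rule should be able to show when the rule has failed. Within T3, depth beyond 5 mm on CT is what separates an eligible tumour from an ineligible one. The stated comparator records T category. If T3 is a single category, the comparator cannot show whether a tumour called deep on CT was deep in the specimen.

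What is at stake is how well the trial can describe its own target population. The Discussion treats a low number of CT false positives as essential, and the statistical section foresees continuation into phase III. As specified, the trial would go forward without having measured how often its 5 mm CT criterion is confirmed on pathology.

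**Working it through.** The article gives no accuracy target or sample size for this endpoint, so there is no stated figure to reproduce. The check is a cross-classification.

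**Inputs**
- CT entry rule: T3 with more than 5 mm extension, T4, and/or N2 (Inclusion criteria, iii).
- Comparator: pTNM, control arm only (Endpoints, vi).
- T3 as one category: Background gives stage II as T3-4/N0/M0. The section on selection of patients by CT scan reports a cited study's accuracy as T3 on CT against T3 on pathology (10 of 14, 71.4 %), with no split at 5 mm.
- Control-arm size: 33 RAS wild-type + 33 RAS mutated = 66 (Statistical analysis and sample size).

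**Control patients who enter only as CT high-risk T3 (not CT T4 or N2)**

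| Specimen | T comparison with pTNM | Entry definition on pathology |
|---|---|---|
| pT1-2 | disagreement | not met, unless pN2 |
| pT3, 5 mm or less | agreement | not met, unless pN2 |
| pT3, more than 5 mm | agreement | met |
| pT4 | disagreement | met |

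The second row is the gap. Those patients count as T agreement although, unless pN2, they fail the entry definition. No row hides an error in the opposite direction among false positives, so the under-count runs one way. It equals the number of such patients and is zero only if there are none.

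**What remains visible.** A CT T4 tumour found to be pT3 is still a mismatch, and so is any nodal discordance. Patients with T4 or N2 disease on pathology meet the definition at any depth.

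**Illustration only.** Every rate here is an assumption; none comes from the article. Let s be the share of the 66 controls entering on T3 depth alone (40 to 80 %), take 5 % of these as pT1-2, let b be the share with pT3 at 5 mm or less (10 to 30 %), and suppose that none of these failures is pN2.
- Patients concerned: 66 × s = 26.4 to 52.8.
- Counted by T category: 26.4 × 0.05 = 1.3 to 52.8 × 0.05 = 2.6.
- Failing the entry definition: 26.4 × (0.05 + 0.10) = 4.0 to 52.8 × (0.05 + 0.30) = 18.5.
- Not counted: 26.4 × 0.10 = 2.6 to 52.8 × 0.30 = 15.8.

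The range is wide because the inputs are unknown. It shows how the count behaves and does not estimate the error.

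**The case against.** The article says that CT staging is compared with pTNM. It does not say that the entry rule is being validated, and a clinical TNM against pathological TNM table is a legitimate like-for-like staging comparison. This stands. No accuracy target is attached, and continuation depends on TRG1 counts, complications and the monitoring committee's recommendations. A reader might infer that the trial could declare CT selection adequate on this endpoint, but the article plans no such step.

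Three further inferences are tempting, and the article does not support them.
- **Failing the 5 mm rule means over-treatment.** The Discussion does not define a false positive by depth. Background describes adjuvant FOLFOX-4 as standard for stage III (any T, N1-2), and Arm C stage III patients are planned to receive chemotherapy. A pT3 tumour at 5 mm or less with N1 nodes fails the entry definition and is still stage III.
- **The comparison would show near-perfect agreement whatever CT does.** For a similar trial the article reports: "T3 or more advanced tumours was pathologically confirmed in 98 % of patients undergoing immediate surgery". That is one dichotomy. The endpoint also covers N stage and T3 against T4, and the studies cited on CT selection include 64 % nodal accuracy.
- **The cited 24 to 30 % over-staging gives the size.** The article does not link that figure to depth within pT3. Over-staging such as pT1-2 read as T3 is an error that pTNM would reveal, so it cannot measure the one that pTNM hides.

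A last objection is that an article condenses the full protocol, which may record depth. The items under (v) concern surgical quality and need not be the whole pathology form. This is fair, and the point does not rest on a missing form field. It rests on the comparator that the article names, which does not match the entry rule that it states.

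**Conclusion.** The point holds as a limited improvement to a secondary endpoint. For control patients who qualify only through T3 depth, the pTNM comparison counts pT3 tumours at 5 mm or less as agreement, so false positives against the trial's own entry definition are under-counted. The direction is certain if pT3 is recorded as a single category, as the article's usage indicates; the article does not say so outright. The size cannot be derived: it depends on how many of the 66 planned controls enter on depth alone and how many of those prove to be 5 mm or less, and neither figure is given. The primary TRG analysis, the sample size and the randomised comparisons are unaffected.

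**What to change.** Keep the clinical against pathological TNM table. Have central pathology also record maximum extramural extension in mm on the control-arm specimens it already reviews for tumour regression. Beside the table, report the proportion of CT-eligible controls who meet the entry definition on pathology: pT3 with more than 5 mm, pT4, and/or pN2. Among those who do not, show node-positive (stage III) patients separately from node-negative ones, so that entry-rule error is not read as over-treatment. If the full protocol already records depth, only the endpoint wording and the extra table are needed.

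The cost is one field on the pathology form for about 66 specimens, one line of endpoint wording and one descriptive table. It needs no additional patients, visits or readers.

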### Endpoints

By evaluating two chemotherapy regimens in patients with *RAS* WT tumor (FOLFOX-4 vs. FOLFOX-4 – Cetuximab), the present trial will determine which neoadjuvant regimen is the most efficient in terms of response rate in patients with non metastatic locally advanced CC.

The primary objective is to assess the histopathological response to neoadjuvant chemotherapy measured by the Tumor Regression Grade (TRG), as simplified to three categories by Ryan [19]. The TRG-Ryan is based on the relationship between fibrosis and the amount of residual tumor cells is defined as follows (Fig. 2). The histopathological finding of fibrous stroma containing few viable tumor cells can be naturally present in almost 10 % of CCs not treated with chemotherapy prior to surgery [15]. Therefore, this parameter represents an objective measure of evaluation in the control (no pre-operative chemotherapy) and study (neoadjuvant chemotherapy) arms. This limits the risk of wrongly concluding therapy efficacy, thereby meeting the methodological standards of a Phase II randomized study. The histopathological response to neoadjuvant chemotherapy will be centrally assessed by 2 of the 3 members of our Central Review Committee of Pathologists who will be blinded to the patients’ treatment. The objective of the blinded comparison of TRG by two independent pathologists is to assess: (i) the inter-observer reproducibility of this grading system in CC after neoadjuvant chemotherapy; (ii) the specificity of histological "regression" criteria by comparing, without knowing the treatment arms, the histological features of tumors operated on immediately versus that of tumors treated by neoadjuvant chemotherapy.

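### Comparing reader agreement on a 3-grade and a 5-grade regression scale can show at most which is more reproducible, not which is most appropriate

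*Protocol article*

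**What the plan says.** Under Endpoints, the primary objective is histopathological response "measured by the Tumor Regression Grade (TRG), as simplified to three categories by Ryan". The secondary endpoint list after Fig. 2 adds, as item (viii), a second scale: "The 5-point regression grading system [22] adapted to CC by our team in a pilot study [15], will also be evaluated". Specimens are graded independently and blind to arm "by 2 of the 3 members of our Central Review Committee of Pathology".

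The last sentence of item (viii) starts from "Comparison of the reproducibility (test of concordance) of the two systems of grading regression" and concludes that this comparison of "TRG-Ryan and TRG-Mandard) will identify the most appropriate system for assessing response to chemotherapy in CC". Concordance is the only criterion in that sentence.

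Three other statements bear on it:

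- For the Ryan scale, Endpoints also plans to assess "the specificity of histological 'regression' criteria by comparing, without knowing the treatment arms, the histological features" of tumours operated on at once and tumours given neoadjuvant chemotherapy. Item (viii) plans a specificity assessment for the five-point scale too.
- Endpoints notes that fibrous stroma with few viable cells can be present in almost 10 % of untreated colon cancers.
- The Discussion, under the heading on histopathological response, says that no such grading system has yet been validated.

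**The concern.** The sentence moves from which scale two pathologists agree on more to which scale is best for measuring response. Two gaps lie between these.

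First, agreement statistics depend on how many grades there are. Fewer grades leave fewer boundaries on which readers can differ, so crude agreement and unweighted kappa tend to rise. Quadratic weights penalise near misses lightly and tend to reward the finer scale. Two scales read with the same precision can therefore be ranked either way.

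Second, a scale can be easy to agree on and still respond poorly to chemotherapy. Some untreated tumours already look regressed and no scale is validated, so reproducibility cannot stand in for validity here.

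At stake is a general conclusion about grading systems in colon cancer that the stated comparison cannot support.

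**Working it through.** The article gives no kappa, target or precision for this comparison, so there is no figure to reproduce. The check is whether two scales read equally well would be ranked equally.

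**Inputs from the article.** Three grades (Ryan) and five grades (adapted Mandard). Two readers per specimen. At most 165 specimens (33 × 3 + 33 × 2). Of these, 99 are in neoadjuvant arms (33 in A and 33 in B for RAS wild type, 33 in A for RAS mutated).

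**Assumptions, not in the article.** Both readers see one underlying regression continuum with the same precision on both scales. Inter-reader correlation is 0.6, 0.7, 0.8 or 0.9. There are five sets of grade shares. In four, the three grades are the five merged 1-2 | 3 | 4-5. In one (set C), the cut-points are unrelated.

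**Formulas.** With p_ij the share graded i by one reader and j by the other, raw agreement is Σ p_ii, and kappa = 1 − Σ w_ij p_ij / Σ w_ij p_i. p_.j. The weights w_ij are 1 for any i ≠ j (unweighted), |i−j| (linear) or (i−j)² (quadratic).

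**One case by hand (set A, correlation 0.8).**

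- Five grades: chance agreement = 0.10² + 0.15² + 3 × 0.25² = 0.220; unweighted kappa = (0.483 − 0.220)/(1 − 0.220) = 0.337.
- Three grades: chance agreement = 0.25² + 0.25² + 0.50² = 0.375; unweighted kappa = (0.668 − 0.375)/(1 − 0.375) = 0.469.

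**All sets at correlation 0.8 (3 grades / 5 grades).**

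| Set | Shares, 5 grades (%) | Shares, 3 grades (%) | Raw agreement | Unweighted | Linear | Quadratic |
|---|---|---|---|---|---|---|
| A | 10/15/25/25/25 | 25/25/50 | 0.668 / 0.483 | 0.469 / 0.337 | 0.580 / 0.568 | 0.680 / 0.746 |
| B | 20 each | 40/20/40 | 0.665 / 0.466 | 0.477 / 0.332 | 0.586 / 0.574 | 0.674 / 0.747 |
| C | 20 each | thirds | 0.648 / 0.466 | 0.471 / 0.332 | 0.580 / 0.574 | 0.689 / 0.747 |
| D | 5/17/38/25/15 | 22/38/40 | 0.661 / 0.525 | 0.477 / 0.357 | 0.575 / 0.558 | 0.683 / 0.735 |
| E | 2/8/15/35/40 | 10/15/75 | 0.778 / 0.578 | 0.453 / 0.387 | 0.550 / 0.560 | 0.641 / 0.725 |

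Over all 20 settings (five sets, four correlations), the three-grade scale was always higher on raw agreement and unweighted kappa, and always lower on quadratic-weighted kappa. On linear-weighted kappa the difference (3 minus 5 grades) ran from −0.013 to +0.018.

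**Chance that the three-grade scale comes out higher in one trial (correlation 0.8, 1,500 simulated trials per set, range over sets).**

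| Specimens | Raw agreement | Unweighted | Linear | Quadratic |
|---|---|---|---|---|
| 99 | about 100 % | 81-100 % | 39-68 % | 1.5-6.5 % |
| 165 | 100 % | 85-100 % | 39-75 % | 0.1-3 % |

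**Size of the handicap.** In sets A to D, five-grade readers need a correlation of about 0.9 (unweighted kappa 0.47-0.52) to come roughly level with three-grade readers at 0.8 (0.47-0.48). The variance not shared between readers must fall from 20 % to 10 %. In set E the handicap is smaller (0.54 at 0.9 against 0.45 at 0.8).

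**The case against.** The strongest reply has four parts.

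- **One sentence in a condensed article states a purpose, and the coefficient may be fixed elsewhere.** This is fair as far as it goes: the unnamed coefficient is not the point. But naming one does not repair the inference. Unweighted or quadratic weights would favour one scale in advance, and no coefficient measures validity.
- **Specificity is already planned for both scales.** That is true and makes the remedy cheap. The concluding sentence still draws its answer from concordance alone.
- **The documents do not say that Ryan grades are merged Mandard grades.** This stands. The claim that merging can never lower raw agreement holds only if one scale is derived from the other. The ordering does not need that link: set C has unrelated cut-points and gives the same result.
- **Linear weights nearly remove the problem.** This stands too. A reader might infer that the choice of statistic always settles the winner. That goes too far: linear weighting gives a near tie with no consistent direction, and a large real difference in reading precision would also count.

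A reader might also infer that this comparison will select the phase III response measure, or that it weakens the primary analysis. The article supports neither. Statistical analysis and sample size bases the phase III decision on TRG1-Ryan counts and the monitoring committee's advice on arms, and nowhere carries the Ryan/Mandard comparison forward.

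**Conclusion.** The stated inference does not hold. With equal reading precision, the ranking of the two scales reverses between unweighted and quadratic-weighted kappa: three grades are ahead by 0.07 to 0.15 on the first and behind by 0.05 to 0.08 on the second, at correlation 0.8. Linear weights leave at most about 0.02 between them. The sizes rest on assumed reader correlations, grade shares and cut-points. The direction was the same throughout the ranges tried, but the argument is exact only where the scales are read with similar precision. Separately from any simulation, concordance says nothing about whether a scale detects chemotherapy effect.

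This is a minor point about one secondary endpoint. The primary endpoint stays fixed as TRG1-Ryan, and no arm decision or sample size depends on the comparison.

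**What to change.** Reword the conclusion of item (viii) in two parts.

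1. **Concordance.** Claim only which system is more reproducible. Name beforehand a coefficient little affected by the number of grades, such as linear-weighted kappa, and give a paired bootstrap confidence interval for the difference, resampling specimens. Other coefficients can be descriptive.
2. **Appropriateness.** Base any such statement jointly on that agreement and on how well each scale, read blind, separates neoadjuvant from control specimens. Do this within RAS stratum, because arm B exists only in RAS wild type.

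Two cautions apply. A comparison at a common major-response cut is supportive only: if one scale is a merge of the other, both reduce to the same yes/no variable and cannot be told apart. Discrimination should be read as separation between arms, not as diagnostic sensitivity, since only 35 % TRG1 is expected after treatment. A ROC area will also tend to favour the finer scale somewhat (0.724 against 0.694 for the same readings, with assumed TRG1 rates of 10 % and 35 %), so it should not decide alone.

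The cost is analysis wording. Blinded central grading on both systems is already planned, so no new data are needed. The downside is that reproducibility alone no longer settles the choice.
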